### End of study definition

The study will be considered closed when all surviving subjects complete in-hospital safety and outcome monitoring. This includes: safety measures of SAE rate within 28 days, total hospital stay, total critical care stays, 28-day ventilator-free days and 28-day mortality

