**Methods/design:**

This multicentre, randomised controlled study will compare the haemostatic effect of an evidence-based VHA-guided versus an optimised CCT-guided transfusion algorithm in haemorrhaging trauma patients. A total of 392 adult trauma patients will be enrolled at major trauma centres. Participants will be eligible if they present with clinical signs of haemorrhagic shock, activate the local massive haemorrhage protocol and initiate first blood transfusion. Enrolled patients will be block randomised per centre to either VHA-guided or CCT-guided transfusion therapy in addition to that therapy delivered as part of standard care, until haemostasis is achieved. Patients will be followed until discharge or 28 days. The primary endpoint is the proportion of subjects alive and free of massive transfusion (less than 10 units of red blood cells) at 24 h. Secondary outcomes include the effect of CCT- versus VHA-guided therapy on organ failure, total hospital and intensive care lengths of stay, health care resources needed and mortality. Surviving patients will be asked to complete a quality of life questionnaire (EuroQol EQ-5D^TM^) at day 90.

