### Secondary endpoints

The secondary endpoints listed below will be analysed in order to provide a sensitive and comprehensive description of outcomes and health care resource demands for the VHA and CCT arm subjects:All-cause mortality at 6 and 24 h and 28 and 90 days post admissionDuration and severity of coagulopathy until haemostasis, as defined by the area under the time multiplied by Prothrombin Ratio (PTr) curve, with coagulopathy defined as PTr > 1.2. Patients who die will have their time of haemostasis set at 24 h, and last PTr extrapolated to this time pointProportion of patients who have corrected coagulopathy, defined as PTr < 1.2, after first 8 units of RBCTime to haemostasis (defined as having occurred at the end of the first hour free of red cell transfusions and the treating clinicians believe primary haemostasis has been achieved)Time spent in coagulopathic condition, defined as PTr ≥ 1.2, until haemostasis, defined as the point 1 h from the last administration of RBC and the treating clinician believes that primary haemostasis has been achievedBlood products administered (RBC, plasma, platelets alone and in total) within first 6 and 24 h after admission28-day ventilator-free and ICU-free days (patients who die in hospital during the 28-day study period will be considered to have zero hospital-free days)Total hospital length of stay28-day symptomatic thromboembolic events defined as: deep venous thrombosis (DVT) diagnosed by compression ultrasound or venography, pulmonary embolism diagnosed by computed tomography (CT) pulmonary angiogram or ventilation-perfusion scan or myocardial infarction and/or stroke identified by standard clinical diagnostic investigation(s)Incidence of transfusion-related complicationsIncidence of organ dysfunction, defined by Sequential Organ Failure Assessment (SOFA) scoreHealth care resource, productivity costs and HRQoL (EuroQol EQ-5DTM at discharge or day 28, and at day 90)Lifetime health economic cost-effectiveness of personalised VHA-guided haemorrhagic treatment versus MTP-based on best practice and CCTs

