#### Schedule of intervention

All participating centres will initiate the management of the study population according to standard local protocols regardless of enrolment in the trial. Following randomisation, study participants will undergo interventions at set time points as outlined in Fig. 1 (Standard Protocol Items: Recommendations for Interventional Trials (SPIRIT) schedule of enrolment, interventions and assessments) and be followed up for 90 days after enrolment.

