#### Patient disposition

First destination after discharge and disposition at 90 days post admission will be recorded as either home, rehabilitation facility, nursing home, other hospital or other.

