#### Quality of life (Qol)

Subject quality of life will be assessed using the EuroQoL EQ-5D^™^ questionnaire, a standardised instrument for use as a measure of health outcome. Quality of life assessment will be conducted in the study centre upon discharge of the subject from hospital and at 90 days post admission.

The in-hospital (i.e. discharge) questionnaire will be conducted by research investigators with the patient where possible, but may also be completed with patient’s PC if necessary. The questionnaire can be completed in less than 5 min. Where the subject has already left hospital, the questionnaire will be posted out with a return stamped addressed envelope.

Patients who have not returned the questionnaire within 2 weeks of the initial request will be telephoned as a reminder to complete the questionnaire and may be asked to complete it over the telephone if necessary.

A further EuroQoL EQ-5D^TM^ questionnaire will be provided to assess subject quality of life at 90 ± 5 days post admission. Confirmation with the local (i.e. hospital care record system) and regional resources (i.e. NHS Health and Social Care Information Centre Spine Services) will ensure that only surviving patients receive a questionnaire.

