#### Method of analysis

All primary and secondary outcomes will be analysed as intention-to-treat, and will include all randomised patients for whom the primary outcome of ‘alive’ and ‘free of massive transfusion’ at 24 h is recorded. The primary endpoint of patients who are alive and free of massive transfusion at 24 h will be assessed by difference in proportion with 95% confidence intervals. The chi-square test or Fischer’s exact test will be used were appropriate. Absolute risk reduction and relative risk reduction by VHA-guided therapy will be calculated.

Kaplan-Meier mortality estimates between the two arms for all-cause mortality at 6 and 24 h, as well as 28 and 90 days post admission, will be estimated for the secondary endpoint of death.

A per-protocol analysis and a sensitivity analysis will be performed for the primary endpoint. The following patients will be excluded from the per-protocol analysis:Patients who do not have at least one ROTEM®/TEG®/CCT test performed *and*
Who die within 60 min after baseline blood sampling *or*
Who achieve haemostasis within 60 min of baseline sampling

Both ROTEM®-guided and TEG®-guided therapy together (i.e. the VHA arm) will be compared with the CCT arm. Separate analyses will be performed for ROTEM®-guided and TEG®-guided therapy alone for primary endpoints and correction of coagulopathy.

All applied tests will be two-sided and *p* values of 0.05 will be accepted as statistically significant. We will report *p* values with and without correction for multiple testing.

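### The end-of-study definition leaves out the day-90 outcomes, so read literally the study can close before the last-enrolled survivors reach day 90

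*Protocol article*

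**What the plan says.** The section End of study definition reads: "The study will be considered closed when all surviving subjects complete in-hospital safety and outcome monitoring". It then names what this covers: "safety measures of SAE rate within 28 days, total hospital stay, total critical care stays, 28-day ventilator-free days and 28-day mortality". No day-90 item is among them.

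Elsewhere the protocol article plans outcomes to day 90:

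- Schedule of intervention: participants will "be followed up for 90 days after enrolment".
- Secondary endpoints: 90-day all-cause mortality, and health-related quality of life by "EuroQol EQ-5DTM at discharge or day 28, and at day 90".
- Patient disposition: "First destination after discharge and disposition at 90 days post admission will be recorded".
- Quality of life: a further questionnaire is provided to "assess subject quality of life at 90 ± 5 days post admission", after hospital and regional records have been checked for survival. For patients who have left hospital, the section describes contact by post, with a telephone reminder.
- Method of analysis: Kaplan-Meier "all-cause mortality at 6 and 24 h, as well as 28 and 90 days post admission, will be estimated".
- Integrated cost-effectiveness analysis: QALYs are built from survival and quality-of-life data.

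The abstract says "Patients will be followed until discharge or 28 days", but also announces an EQ-5D at day 90 for survivors.

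Patients who withdraw after randomisation are followed for safety to the end of day 28, and longer only for an ongoing serious adverse event (Data collection and follow-up for withdrawn subjects).

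**The concern.** An end-of-study definition normally marks the point at which every planned outcome has been obtained. This one is met earlier than the plan's own longest outcomes. A site or sponsor acting on it could close the study with day-90 mortality, disposition and EQ-5D still outstanding for the most recently enrolled survivors. The day-90 questionnaire is most exposed, because for discharged patients it depends on active contact after the hospital stay. The precision of the 90-day mortality estimate and the quality-of-life input to the QALYs would also suffer.

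A related gap concerns withdrawn patients and does not depend on the closure date. Subject withdrawal allows removal for retrospective ineligibility, major protocol deviation or investigator discretion, as well as for withdrawn consent. Many such patients need not have refused follow-up. Method of analysis promises intention-to-treat analysis of all secondary outcomes for randomised patients whose 24 h outcome is recorded, yet the commitment for withdrawn patients is safety follow-up to day 28. Missing 90-day status in this group could be related to prognosis and could differ between arms, because clinical staff and site investigators are not blinded.

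**Working it through.** **1. Time points side by side**

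| Item | Latest time point | Section |
|---|---|---|
| Serious adverse events, ventilator-free days, mortality in the closure list | day 28 | End of study definition |
| Hospital and critical care stay in the closure list | discharge, no cap | End of study definition |
| All-cause mortality | day 90 | Secondary endpoints; Method of analysis |
| Disposition | day 90 | Patient disposition |
| EQ-5D | day 90 ± 5 | Secondary endpoints; Quality of life |
| Follow-up of participants | 90 days | Schedule of intervention |

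The definition can be met no earlier than day 28 of the last enrolled survivor. The gap to day 90 is then 90 − 28 = 62 days. With the EQ-5D window it is 85 − 28 = 57 to 95 − 28 = 67 days.

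**2. The plan's own figure**

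The only computed figure in the article is the sample size. For 28% against 15%, 80% power and two-sided alpha 0.05, the standard formula gives 156 per group without and 171 with continuity correction, so the stated 170 is close to the corrected value. Dropout: 170 / (1 − 0.13) = 195.4, rounded up to 196 per arm, or 392 in total, as stated. The point here uses only the total of 392.

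**3. Patients short of day 90 at closure**

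Inputs: 392 patients (Sample size); recruitment from June 2016 to mid 2018 (Trial status). Assumptions: even accrual, and a recruitment period M of about 24 months with a range of 22 to 26. Let c be the number of days from the last enrolment to closure, with c at least 28.

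Number short of day 90 = 392 / (M × 30.4375) × (90 − c)

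| M (months) | c (days) | Per month | Number short of day 90 | Share of 392 |
|---|---|---|---|---|
| 22 | 28 | 17.8 | 36.3 | 9.3% |
| 24 | 28 | 16.3 | 33.3 | 8.5% |
| 26 | 28 | 15.1 | 30.7 | 7.8% |
| 24 | 60 (assumed last discharge) | 16.3 | 16.1 | 4.1% |
| any | 90 or more | – | 0 | 0% |

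Counting to the end of the EQ-5D window (day 95) with M = 24 and c = 28 gives 392 / 730.5 × 67 = 36.0.

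These are randomised patients. Those who died before closure are included in the count, but their mortality status is known and they need no questionnaire, so the number with an outcome outstanding is smaller. The article does not give the figures needed to subtract them.

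**4. Withdrawn patients**

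No count can be derived. The dropout allowance is 392 − 2 × 170 = 52 patients, but the article does not say how many of these would be withdrawals without day-90 status.

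**The case against.** The strongest reply is that loss of data is inferred. The definition says when the study counts as closed; it does not say that collection stops then or that later data are left out. The 90-day follow-up in Schedule of intervention makes no exception for late enrolment, and the EQ-5D section sets out a working day-90 procedure. This stands. A reader might infer that the plan discards the last patients' day-90 data, but the document does not support that. What remains is that the definition has to be disregarded to obtain endpoints the plan lists.

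The closure list may also be illustrative, and it already contains 28-day mortality, which for early discharges is a post-discharge outcome. That loosens the wording, but no day-90 item is named and the rule is framed around the hospital stay.

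Hospital stay has no cap, so closure waits for the longest-staying survivor and may fall well after day 28. This stands too. Under even accrual, 31 to 36 is therefore a ceiling, not an expected loss. Nothing in the definition ensures, however, that closure waits until day 90.

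Two further inferences should be resisted. The abstract does not simply stop at 28 days, since it also announces the day-90 EQ-5D; its follow-up sentence needs aligning but is weak evidence. Nor is there a basis for saying that the centres due to start in 2017 would lose most: the final weeks of recruitment affect every centre still recruiting.

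On withdrawals, it can be said that a 28-day safety window matches the 28-day safety measures and that further collection is a consent matter. The text does not forbid later collection. But withdrawal here is wider than refusal, and the intention-to-treat commitment extends to 90-day mortality.

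**Conclusion.** The inconsistency is real and lies within the current text: the closure rule omits day-90 mortality, disposition and EQ-5D, which five other sections of the article's methods require. Its consequence is a risk to secondary and economic outcomes. The 24 h primary endpoint, the sample size and outcomes to day 28 are unaffected.

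The size is at most about 31 to 36 of 392 patients (8% to 9%) short of day 90. This rests on even accrual over an assumed 22 to 26 months and closure 28 days after the last enrolment. The figure falls with later closure and with deaths already recorded; it would rise if accrual were heavier towards the end, on which the article gives no data. For mortality, Kaplan-Meier estimation can handle administrative censoring at closure, so the cost there is mainly precision. A missing EQ-5D or disposition has no such remedy.

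The withdrawn-patient gap is a smaller, separate matter of bias in 90-day mortality, of unknown size. The point is worth correcting because the correction is cheap, not because the trial's main result is at stake.

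**What to change.** - Define end of study as completion of the day-90 (± 5 days) assessment, or death, of the last randomised patient.
- Align the abstract's follow-up sentence with the 90 days in Schedule of intervention.
- State that day-90 vital status will be collected for withdrawn patients who do not refuse it, so that the intention-to-treat analysis of 90-day mortality can include them.

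The cost is an amendment to one definition and two short text changes, formal closure up to about two months later (62 days, or 67 to the end of the EQ-5D window), and a small amount of record checking. The 90-day follow-up itself is already planned, and the sample size does not change.

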### Statistical considerations

#### Sample size

Based upon legacy registry data from the partners, approximately 28% of patients will need massive transfusion or die. It is expected that this figure will decrease to an overall proportion of 15% in the VHA group (i.e. using VHA-guided strategy). In order to detect a difference from 28% to 15% with a power of 80% and a two-sided alpha of 0.05, 170 patients per group are required. One hundred and ninety-six patients per study arm allows a 13% dropout rate, with an allocation ratio of 1. The planned sample size for this study is 392 patients for which MTP is activated and transfusions initiated, 196 in each study arm.

#### Method of analysis

All primary and secondary outcomes will be analysed as intention-to-treat, and will include all randomised patients for whom the primary outcome of ‘alive’ and ‘free of massive transfusion’ at 24 h is recorded. The primary endpoint of patients who are alive and free of massive transfusion at 24 h will be assessed by difference in proportion with 95% confidence intervals. The chi-square test or Fischer’s exact test will be used were appropriate. Absolute risk reduction and relative risk reduction by VHA-guided therapy will be calculated.

Kaplan-Meier mortality estimates between the two arms for all-cause mortality at 6 and 24 h, as well as 28 and 90 days post admission, will be estimated for the secondary endpoint of death.

A per-protocol analysis and a sensitivity analysis will be performed for the primary endpoint. The following patients will be excluded from the per-protocol analysis:Patients who do not have at least one ROTEM®/TEG®/CCT test performed *and*
Who die within 60 min after baseline blood sampling *or*
Who achieve haemostasis within 60 min of baseline sampling

Both ROTEM®-guided and TEG®-guided therapy together (i.e. the VHA arm) will be compared with the CCT arm. Separate analyses will be performed for ROTEM®-guided and TEG®-guided therapy alone for primary endpoints and correction of coagulopathy.

All applied tests will be two-sided and *p* values of 0.05 will be accepted as statistically significant. We will report *p* values with and without correction for multiple testing.

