#### Randomisation procedure

Enrolled patients will be block randomised per centre to either the CCT or the VHA study arm within 3 h of injury and within 1 h of admission. The trial will be un-blinded for clinical staff and site investigators. Once a patient is determined eligible for the study and informed consent or agreement has been obtained, each subject will be enrolled as soon as possible and will be assigned a unique alphanumeric study identifier. Randomisation will be performed by the site investigator opening a sealed envelope containing the randomised treatment group, to allow for immediate allocation of subjects. An independent party, appointed by the sponsor, will generate the randomisation sequence and site envelopes centrally.

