### Randomised study care – VHA arm

VHA will be conducted for all subjects in the VHA arm at each time point up to 24 h. During active haemorrhage, samples will be taken for VHA analysis at baseline and after every 4 units of RBC until haemostasis. The clinical course of subjects randomised to the VHA arm will follow a treatment algorithm utilizing VHA results (Fig. 3a and b). The subject will be treated with standard haemostatic resuscitation based on a MTP aiming for 1:1:1 ratio of blood components and initial TXA. In addition, according to threshold values in the algorithms, the subjects will be given fibrinogen concentrate or cryoprecipitate and/or additional platelets, plasma and TXA depending on the VHA results.

Fibrinogen concentrate or cryoprecipitate will be administrated when FIBTEM Clot Amplitude at 5 min (CA5) is below 10 mm or functional fibrinogen (FF) TEG® Maximum Amplitude (MA) is below 20 mm. Additional platelets are indicated when the subtracted amplitude of FIBTEM CA5 from EXTEM CA5 is below 30 mm, or the subtracted amplitude of FF TEG® MA from rapid TEG® MA is below 45 mm. Additional plasma is indicated when the results show a normal EXTEM CA5, defined as above 40 mm, but still a prolonged EXTEM clotting time (CT), defined as above 80 s, or normal rapid TEG® MA, defined as above 65 mm, but still a prolonged rapid TEG® activated clotting time (ACT), defined as above 120 s. Additional TXA is indicated when the EXTEM Lysis Index at 30 min (LI30) is below 85% or rapid TEG® clot lysis at 30 min (Ly30) is above 10%.

This VHA treatment algorithm is based upon analysis of more than 2200 trauma subjects enrolled to a prospective observational study conducted at the participating study sites, entitled Activation of Coagulation and Inflammation in Trauma (ACIT). Analysis of the ACIT dataset has enabled the definition of clinically relevant VHA thresholds and patterns by which it is possible to rapidly identify coagulopathic patients and anticipate the need for massive transfusion. These threshold parameters have been applied to the generation of an evidence-based targeted treatment algorithm.

According to pre-designation, each study centre will only conduct VHA using either thromboelastography (TEG®) or rotational thromboelastometry (ROTEM®) to determine the following parameters:TEG®: RapidTEG® ACT, MA and Ly30; functional fibrinogen TEG® MAROTEM®: EXTEM CT, CA5 and Li30; FIBTEM CA5

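### The named primary test ignores the centre blocks, and the ROTEM and TEG analyses do not fix a same-centre CCT comparator

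*Protocol article*

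**What the plan says.** **Randomisation.** The section on randomisation states: "Enrolled patients will be block randomised per centre to either the CCT or the VHA study arm". The opening of Methods/design lists eight trauma centres.

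**Device.** The section on the VHA arm fixes the device for every site in advance: "each study centre will only conduct VHA using either thromboelastography (TEG®) or rotational thromboelastometry (ROTEM". Device is therefore a property of the centre and was not randomised.

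**Primary analysis.** Method of analysis says: "The primary endpoint of patients who are alive and free of massive transfusion at 24 h will be assessed by difference in proportion". The test named is chi-square or Fisher exact, and a 95% interval is to be reported. Neither stratification nor adjustment for centre is mentioned.

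**Device analyses.** The same section first compares the two devices pooled, as the VHA arm, with the CCT arm. The next sentence reads: "Separate analyses will be performed for ROTEM®-guided and TEG®-guided therapy alone for primary endpoints and correction of coagulopathy". It does not say which CCT patients serve as comparator.

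**Centre differences.** Adult status and activation of the haemorrhage protocol follow local rules (Inclusion criteria), as do transfusion triggers (Screening procedures). The baseline transfusion protocol is standardised only as far as local routines and product supply permit (Standard care).

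**The concern.** Two consequences follow from a design stratified by centre and an analysis that is not.

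First, blocking within centre removes between-centre variation from the treatment contrast. A crude test still counts that variation in its standard error, so the interval for the primary endpoint is a little too wide and the test a little too cautious.

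Second, the comparator decides whether a device analysis is randomised. ROTEM-guided patients come only from ROTEM centres. Against CCT patients at those centres, the comparison is protected by randomisation. Against the whole CCT arm, it sets some hospitals against all hospitals, and a difference in case mix or local practice can appear as a device effect. The device analyses cover the primary endpoint and correction of coagulopathy. The two devices also have different parameters and thresholds in the protocol, so readers will take these results as evidence on each algorithm.

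**Working it through.** **Inputs from the protocol (Sample size).** Control event rate: "approximately 28% of patients will need massive transfusion or die". VHA arm: "this figure will decrease to an overall proportion of 15% in the VHA group". Then: "with a power of 80% and a two-sided alpha of 0.05, 170 patients per group are required". Enrolment: "One hundred and ninety-six patients per study arm allows a 13% dropout rate, with an allocation ratio of 1".

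**The plan's own figure.** With p1 = 0.28, p2 = 0.15 and mean 0.215:

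n = [1.96·√(2·0.215·0.785) + 0.8416·√(0.28·0.72 + 0.15·0.85)]² / 0.13² = (1.1387 + 0.4828)² / 0.0169 = 155.6, so 156 per arm.

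With continuity correction: (155.6/4)·[1 + √(1 + 4/(155.6·0.13))]² = 170.6, so 171. The stated 170 is reproduced to within one patient. Dropout: 170/0.87 = 195.4, so 196. The sample size is not in dispute.

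**Assumptions.** The protocol gives no centre event rates, centre sizes or number of centres per device. All are assumed below.

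**Primary comparison, 28% v 15%, eight equal centres.** Crude chi-square against the Cochran-Mantel-Haenszel (CMH) test stratified by centre. SD is the between-centre standard deviation on the logit scale.

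| SD | Control rates by centre | Per arm | Power crude / CMH | Type I error crude / CMH |
|---|---|---|---|---|
| 0 | 28% | 192 | 87.7 / 87.8% | 4.8 / 4.8% |
| 0.3 | 19–39% | 192 | 88.1 / 88.4% | 4.7 / 4.9% |
| 0.5 | 14–46% | 192 | 88.6 / 89.4% | 4.4 / 5.0% |
| 0.8 | 8–56% | 192 | 88.8 / 90.7% | 3.8 / 5.0% |
| 1.0 | 6–63% | 192 | 89.5 / 92.0% | 3.1 / 4.9% |
| 1.0 | 6–63% | 168 | 85.2 / 88.2% | 3.4 / 5.2% |

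A separate simulation drew centre effects at random, with 170 per arm in total. At SD 0.5 it gave power 84.4 v 85.0% and crude type I error 4.5%. At SD 0.8 it gave 84.6 v 86.2% and 4.1%. For SD 0.5 to 1.0 the loss is thus 0.6 to 2.5 points, and 3.0 in the last row of the table.

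**Device comparison, no true effect.** 24 patients per arm per centre, overall rate 28%, centres allotted to devices at random. Type I error of ROTEM-guided patients against all CCT patients:

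| ROTEM centres | SD 0 | SD 0.3 | SD 0.5 | SD 0.8 |
|---|---|---|---|---|
| 4 of 8 | 5.0% | 6.8% | 9.6% | 15.7% |
| 5 of 8 | 5.2% | 6.0% | 7.7% | 12.0% |
| 6 of 8 | 5.1% | 5.3% | 6.6% | 8.8% |

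With same-centre CCT patients as comparator there is no bias, and type I error is 4.3 to 4.8% in the 4/4 split (3.9 to 5.2% over all splits).

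The lower rows describe the device used at more centres. With equal centres and a 6/2 split, the two biases satisfy 6·b(ROTEM) + 2·b(TEG) = 0, so the two-centre device carries three times the bias.

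**Fixed example.** Assume event rates of 24% at ROTEM and 32% at TEG centres in both arms, with 98 VHA patients per device and 196 CCT patients.

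- Pooled CCT rate: (24 + 32)/2 = 28%. Spurious difference for ROTEM: 24 − 28 = −4 points; for TEG: +4 points.
- Standard error of the difference: √(0.24·0.76/98 + 0.20/196) = 0.054, where 0.20 is the mean of 0.24·0.76 and 0.32·0.68. The shift is 0.04/0.054 = 0.74 standard errors.
- Simulated type I error: 11.0% (ROTEM) and 11.4% (TEG).
- At 20% and 36% the shift is 8 points and the error 31.5% and 29.2%.
- Same-centre comparator: 5.1%.

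**The case against.** The strongest reply is that the device sentence names no comparator. The CCT arm is named in the sentence before, which defines the pooled comparison. Repeating that comparison within ROTEM centres and within TEG centres fits the wording equally well, and it would be fully randomised. This stands. A reader might infer that the device comparisons are confounded as planned. The protocol does not say so; it only leaves that analysis open, in wording that invites it.

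A second reply is that the primary analysis is hardly harmed. This also stands. A reader might infer that the crude test is biased or leaves the trial short of power. It does neither: the error is on the cautious side, and power stays above the planned 80% in every run.

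Third, the larger figures depend on assumed gaps between centres. Equal centre sizes are doubtful, since two of the eight centres were still planning to start recruitment in 2017. The protocol also describes steps that narrow centre differences: a common 1:1:1 protocol introduced about two months before the trial, and the same products in both arms. This limits the size of the effect but not its direction.

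Last, the full protocol or a statistical analysis plan, neither shown here, may settle both matters. That would excuse silence. It does not fully answer a document that names an unstratified test and announces the device analyses in ambiguous terms.

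**Conclusion.** The point holds in a limited form. The analysis named does not follow the stratified design, and the device analyses lack a stated same-centre comparator.

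For the primary endpoint the effect is small and conservative. Type I error is about 3 to 4.5% and the power loss about 0.6 to 2.5 points (3.0 at most) for logit SD 0.5 to 1.0, with smaller effects below that. There is no bias.

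For the device analyses the effect is conditional. If the comparator is the whole CCT arm, type I error is about 7 to 16% with a 4/4 split and logit SD 0.3 to 0.8. About 30% arises only with an assumed 16-point gap between the device groups. If the comparator is CCT patients at the same centres, it is about 5%. Any direct ROTEM-versus-TEG contrast is non-randomised whichever comparator is used.

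**What to change.** 1. **Primary analysis.** Report a centre-stratified Mantel-Haenszel risk difference with 95% confidence interval and a Cochran-Mantel-Haenszel test. State in advance how very small centres are pooled, for example by country.
2. **Device analyses.** Compare ROTEM-guided patients only with CCT patients at ROTEM centres, and TEG-guided patients only with CCT patients at TEG centres, each stratified by centre.
3. **Interpretation.** State that any ROTEM-versus-TEG contrast, including a difference between the two device effects, is not a randomised comparison of devices.

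**Cost.** Only the wording changes. No patients or data are added, because centre is known from the randomisation. The price is a smaller comparator for each device. With an assumed 98 VHA patients per device, 98 instead of 196 CCT patients widens the interval by a factor of about √[(1/98 + 1/98)/(1/98 + 1/196)] = √(2/1.5) = 1.15. Power for 28% v 15% at 98 per arm is then about 60%, so the device results should be presented as supportive.
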